### 3.6.E. DRIED BLOOD SPOTS

Dried blood spots (DBS) will be collected at each study visit for phosphatidylethanol (PEth) testing, which will be conducted at the United States Drug Testing Laboratories, Inc. (USDTL).

## 4. STUDY PROCEDURES

### 4.1 RECRUITMENT

Participants will be recruited from the following sources:

- Russia ARCH cohort (U01AA020780)
- Notification of patients at clinical and non-clinical sites of care affiliated with Pavlov State Medical University (PSMU) through distribution of study flyers. These sites include Botkin Infectious Disease Hospital, St. Petersburg AIDS Center, City Addiction Hospital and local non-governmental organizations (NGOs) serving HIV-positive persons. Staff at these sites will be informed about the study and asked to refer interested and potentially eligible persons to our recruitment site (Pavlov Medical University) for phone or in-person screening by our study research team.
- Participant database of our laboratory at Pavlov Medical University
- Enrolled participants (i.e. snowball recruitment). Enrolled participants will be given information sheets to distribute to potential participants who might be interested and qualified. Interested

potential participants will be responsible for directly contacting study staff listed on the information sheet to be screened for eligibility.

## 4.2 SCREENING

Existing Russia ARCH participants will be offered an opportunity to be screened for ZINC during one of their ARCH study-related contacts (phone or in-person); in addition, some individuals will be screened for Russia ARCH and ZINC simultaneously.

If an interested participant reaches out to the study team (or is reached by study team) via phone or in-person (Pavlov University), the RA will administer a verbal consent for the screening process, which will include a brief description of the study. Following receipt of verbal consent the RA will screen the participant to confirm eligibility. All responses to the screener will be entered directly into an electronic data capture system by the RA. Screening for the study will occur in two steps: A (verbal) and B (with documentation).

To ensure that double enrollment does not occur, prior to screening, the assessor will search in the electronic system for the last name of the potential participant. If the name does not already exist in the system, the assessor will proceed with screening the participant. If the name exists in the system, the assessor will compare the first name, age and gender of the potential participant with that of the participant with the same last name to determine if the individual has already been enrolled (this will be done very confidentially, ensuring that the potential participant will not be able to ascertain that there is someone with the same last name already in the study, to protect the confidentiality of the enrolled participant). If all of these characteristics match, but the individual says they never enrolled before, the assessor will contact the Russian study supervisor prior to enrollment to determine whether or not this person was previously enrolled.

The RA will administer ZINC screener A to confirm the participant's age; ART-status; that the participant is not currently pregnant or breastfeeding; that the participant has a home or mobile telephone; and lives within 100 kilometers of St. Petersburg. The RA will also ask about the participant's quantity and frequency of drinking in the past 30 days.

Once a participant is confirmed to meet study entry criteria (screening A), they will be scheduled for their first study visit (screening B and baseline). If the participant was already enrolled in ARCH, but new to ZINC, their baseline visit will be scheduled to coincide with an ARCH follow-up visit. If the participant is new to both ARCH and ZINC, an RA will call to remind the participant of their visit both one week and 24 hours before their scheduled appointment (if time allows).

When the participant arrives at Pavlov University for their baseline visit, the RA will re-screen the participant to assess ART use, pregnancy and breastfeeding status, and confirm HIV and ART status (screening B). As part of screening B, participants will be required to provide documentation of HIV and ART-naïve status. This documentation will take form of letters from a medical provider, laboratory results and excerpts from medical histories.

A 30-day window is allowed between screener A and screener B/baseline. Participants who are unable to return to the laboratory within 30 days (either due to scheduling or inability to obtain documentation) will re-initiate the screening process with screening consent and screener A.

Participants who are found ineligible at either stage (screener A or B) will be thanked for their time and will receive a listing of local addiction and HIV care resources. Data collected on participants who "screen out" will be kept in order to have an accurate record of the rate of enrollment among participants screened for participation, and to be able to identify reasons why potential participants are ineligible. The data will not contain identifying information.

#### 4.3 INFORMED CONSENT

After eligibility and interest in enrollment is determined, a research assessor will administer and document the informed consent of the participant. If the potential participant needs time to consider participating, the RA will provide his/her contact information to the participant. If the RA has not heard from the participant 3 days after the initial screening, s/he will call the participant back to ask about participating. If the participant is still not ready to accept or refuse participation, s/he will be able to call the RA at anytime but will need to be re-screened. The study will be explained to eligible participants and research assessors will answer any questions the participants have, including risks, benefits and alternatives (including non-participation) to participation, and will provide written materials describing the study. The written informed consent (in Russian), including the risks, benefits and alternatives, will be signed by the participant and the research assessor. As part of the informed consent process, it will be made explicit to the participants that their involvement in the study will not constitute medical treatment and that they would not receive any medical care (HIV or addiction) as part of the study. A handout will be provided with information on addiction and HIV treatment services to participants at the baseline visit. A copy of the informed consent will be provided to the participant and a copy will be maintained by the research team. Potential participants will be informed that refusal to participate would not affect their medical care at PSMU in any way and they will be informed of their right to drop out of the study at any time.

Once the participant signs the informed consent form, the RA will finalize and complete the Consent and Enrollment Form electronically.

#### 4.4 VISIT FLOW

##### **Baseline:**

Participants will be asked to complete a baseline assessment immediately after signing the informed consent. The baseline assessment will include a face-to-face- questionnaire and collection of blood from participants.

The baseline assessment will take between one and two hours to complete.

#### **Follow Up Assessment:**

The assessor will administer the Symptom Monitoring Form. Following this, a urine sample will be collected. The urine sample will be tested for pregnancy and assessed for color change using a UV light. Results will be recorded in the ZINC Medication Adherence Form. The assessor will conduct the study assessment and send the participant for a blood draw. The face-to-face interview for the 6, 12, and 18-month follow up assessment will follow the same protocol as the baseline assessment in that there will be an interviewer-administered portion and a participant self-administered portion.

#### **Medication Visits:**

At the medication visits, the assessor will update the participant's Contact/Locator form and verify any new numbers. The assessor will complete a Symptom Monitoring Form. If the participant is female, she will be asked if she is currently pregnant. Participants will be asked if they had seen a doctor, visited an emergency room, or if they were hospitalized since their last visit. The assessor will collect information on the participant's current medication use. The assessor will collect a urine sample from the participant, check the urine color, and test all females for pregnancy. As in the longer follow-up assessment visits, sections on Medication Adherence (and count of study pills returned by the participant) and ART Medication History will be administered. The assessor will reinforce the study medication instructions and the medication adherence plan. Participants will be given study medication. At the time of the 6-week medication visit, some participants will also be sent for a fibroscan, if this procedure is indicated based on their FIB-4 score (see section 3.6.D Liver Status).

### **4.5 QUALITY ASSURANCE**

#### **Informed consent quality assurance:**

The RA will review Informed Consent Forms (ICFs) for completeness with the participant present. Items to check include, but are not limited to: responses/initials collected for all questions, correct version of ICF used, signed and dated by both participant and RA. The project manager will review ICFs weekly for completeness.

#### **Assessment quality assurance:**

Certain quality assurance checks will be built into the assessment. The system will flag any inappropriate responses and prevent the RA from continuing until the issue is resolved.

On the day of the study visit, the research assessor will review the entire completed assessment and address any issues. Within two weeks of completion of the study visit, the data manager or supervisor will review the entire completed assessment and address any issues.

#### 4.6 COMPENSATION

Participants in the trial will receive the equivalent of US \$40 in goods or cash for their participation at baseline, 6, 12 and 18 months, which involve the collection of blood for laboratory testing. Participants will also receive compensation equivalent to US \$14 (500rub) for short adherence check visits at 6 weeks, 12 weeks, 9 months, and 15 months where medication was dispensed and urine collected for zinc/riboflavin adherence checks. For follow-up assessments that occur on the phone (rather than in person), participants will receive partial (1/2) compensation, as they will not be compensated for travel time or transportation costs, and a phone interview takes less time to complete than an in-person interview. Similar compensation was used in a previous collaborative Russian-Boston research study and was deemed by the PSMU IRB to be an appropriate, non-coercive, amount of funds for involvement in a clinical research project. Participants who refer individuals who enroll in the study will receive 300 rubles (approximately \$5USD). Participants who provide updated contact information to research assessors in between research visits (i.e. not during the research assessment) will receive 200 rubles in goods or currency. We will also provide an equivalent of 300 rubles in telephone minutes or other goods or currency for enrollment anniversaries.

#### 4.7 RETENTION

Retention begins at baseline by ensuring that the participant enjoys the experience of participating in the study, by explaining the informed consent and what would happen in the study, and by collecting good contact information. Participants will be asked to provide contact information for 2-3 alternative contacts who may know their whereabouts. Contact numbers will be verified by calling the numbers with the participant present. Participants will be contacted by telephone with appointment reminders and email will be used if one is provided.

The study team will also utilize social networking to connect with participants. If participants can not be reached via phone, in addition to attempting to reach them via text messaging and email, participants will be sent private messages on Vkontakte (Russian social network) utilizing an existing standard script to remind them of their upcoming study visit. No sensitive information will be revealed or ascertained using this method.

Appointment information will be kept up-to-date in the tracking system, so that automatic text messages are accurate. Contact information will be updated at every visit. Study participants will be asked to contact the study team if their phone number changed between study visits; participants will be compensated for this information. All no-shows will be followed up with to reschedule appointments.

Participants will be offered tea, coffee, water, and snacks at each study visit to make their experience in the research study more enjoyable.

In the event that a participant becomes incarcerated during the study period, the participant will not be withdrawn from the study, but kept on a separate list. Incarcerated participants will be called twice per

672 year in January and August to determine if they have been released and could continue with study  
673 procedures.

674 Additional retention strategies to improve study follow-up:

- 675 •The study team will send letters to participants, whom the study team is continually unable to reach,  
676 asking them to contact the study team. In the letter, compensation will be offered to participants 300  
677 RUB(\$5) for calling the study team and updating their contact information. The letter will explicitly state  
678 that additional compensation would be received when the participant came in for their scheduled study  
679 visit.
- 680 •Participants will be paid 200 Russian rubles in goods or currency for providing the study team with  
681 updated contact information in between research visits.
- 682 •In order to celebrate continued participant engagement, we will provide an equivalent of 300 rub  
683 (approximately \$5) in telephone minutes or other goods or currency for enrollment anniversaries (i.e.  
684 12-month visit).
- 685 •Assessors will wish participants a happy birthday during reminder calls near their date of birth.  
686 Participants will also receive sweets when they come in to complete a study visit near the time of major  
687 Russian holidays (i.e. New Year, Christmas).
- 688 •The team will collaborate with the City Addiction Hospital (CAH) in their retention and follow up efforts.  
689 Assessors will be able to contact staff at the CAH to find out if participants were hospitalized there. If  
690 participants are found to be hospitalized at the CAH, assessors will be able to receive updated contact  
691 information for these participants and contact them directly by phone to schedule an appointment post  
692 hospitalization.

693 Reminders:

694 One month before each follow-up interview, participants will be contacted by telephone to confirm the  
695 date and time of their appointment and to inform them that a call would be made the day before their  
696 appointment as a reminder. If a participant cannot be reached (e.g. phone is not in service), an email will  
697 be sent to the participant and other participant contacts will be called for updated information.

698 One week before each follow-up interview, participants will be contacted by telephone to confirm the  
699 date and time of their appointment and to inform them that a call would be made the day before their  
700 appointment as a reminder. If the participant cannot be reached (e.g. phone is not in service), an email  
701 will be sent to the participant and other contacts called for updated information.

702 72 hours before each follow-up interview, an SMS will be sent to remind the participant of their visit.

703 24 hours before each follow-up interview if the participant did not respond to SMS, a call will be made to  
704 remind the participant of the time and location of their appointment.

705 If a participant does not show up to the appointment, the participant will be called on the same day to  
706 reschedule their appointment. Calls will be made continuously until the participant can be reached.

Contacting participants over the phone is preferred. If participants are not able to be reached by phone, an SMS and email message will be sent to the participant, unless the participant opts out of receiving text messages at baseline.

Note: Confirmation of receipt from participant must be received in order for a message to be considered delivered. If no confirmation is received, it should be assumed that the participant was not reached.

Standard Text for Study Visit Reminders:

SMS: This is a reminder that your visit to Pavlov Medical University is scheduled for \_\_\_\_ at \_\_\_\_\_. Please reply to confirm or call [name] to reschedule.

E-Mail: This is a reminder that your visit to Pavlov Medical University is scheduled for \_\_\_\_ at \_\_\_\_\_. Please reply to confirm or call [name] to reschedule.

## **5. ASSESSMENTS**

### **5.1 BASELINE ASSESSMENT**

The baseline assessment will be conducted immediately following the screening, informed consent, and blood draw. Assessment will be interviewer-administered with the exception of sections deemed to ask sensitive questions, which will be self-administered by the participant. At baseline the following surveys will be administered: Demographics; HIV Testing and HCV Diagnosis; Co-Morbidities; Russian Brief Pain Inventory; Medications; Zinc intake; HIV Symptom Index; The Center for Epidemiologic Studies Depression Scale (CES-D); Emotional Health: International Personality Item Pool (IPIP) and the Revised Life Orientation Test (LOT-R); The Fagerström Test for Nicotine Dependence; Alcohol Surrogates; MINI: Alcohol Dependence/Abuse; 30 Day Timeline Follow Back; Drug Use (modified Risk Behavior Survey); 24 Hour Activities; Social Support Scale; and VR-12 Health Survey.

### **5.2 FOLLOW UP ASSESSMENTS**

The 6-, 12- and 18-month ZINC assessments contain the same sections as the baseline assessment with the addition of questions on Medication Adherence; Medication Satisfaction; ART Use and Adherence; and Opportunistic Infections. The MINI: Alcohol Dependence/Abuse section are omitted from 6-, 12- and 18-month assessments. Questions on Medication Adherence and Medication Satisfaction are also asked at shorter medication visits.

#### **5.2.A. MEDICATION VISITS ASSESSMENTS**

Medication symptoms and questions on Medication Adherence and Medication Satisfaction are also asked at shorter medication visits.

6. PARTICIPANT SAFETY

ZINC AE/SAE Flow Chart

[figure not shown]

An **Adverse Event (AE)** is defined as any untoward or unfavorable medical occurrence in a human subject, including any abnormal sign (for example, abnormal physical exam or laboratory finding), symptom, or disease, temporally associated with the subject's participation in the research, whether or not considered related to the subject's participation in the research.

An AE can therefore be any new sign, reaction, symptom, event, disease or a worsening in frequency or severity of a preexisting condition that occurs during the course of the study.

Stable chronic conditions that were present prior to study entry and do not worsen are not considered AEs.

**SERIOUS Adverse Event** – for an event to be defined as serious it will be Grade 1-6 below. Grade 0 would be “not serious”.

Grade (1) results in death;

Grade (2) is life-threatening (places the subject at immediate risk of death from the event as it occurred);

Grade (3) results in inpatient hospitalization or prolongation of existing hospitalization;

Grade (4) results in a persistent or significant disability/incapacity;

Grade (5) results in a congenital anomaly/birth defect; or

Grade (6) based upon appropriate medical judgment, may jeopardize the subject's health and may require medical or surgical intervention to prevent one of the other outcomes listed in this definition (examples of such events include allergic bronchospasm requiring intensive treatment in the emergency room or at home, blood dyscrasias or convulsions that do not result in inpatient hospitalization, or the development of drug dependency or drug abuse).

**Unanticipated Problem**- for an event to be an Unanticipated Problem it must be unexpected AND

be related or possibly related to participation in the research AND

suggest that the research places subjects or others at a greater risk of harm (including physical, psychological, economic, or social harm) than was previously known or recognized. OR meet the definition of **SERIOUS**

**Suspected Adverse Drug Reaction** – Any adverse event for which there is a reasonable possibility that the drug caused the adverse event. Reasonable possibility means there is evidence to suspect a causal relationship. It is considered unexpected if it is not consistent with the risk information described in the

general investigational plan. A suspected adverse drug reaction will be defined as a recorded adverse event that is unexpected and deemed to be possibly, probably, or definitely related to the study drug.

## 6.2 THE METHODS AND TIME FOR ASSESSING, RECORDING, AND ANALYZING SAFETY PARAMETERS

- Participant symptoms will be assessed at baseline to document any chronic conditions or symptoms that existed prior to introduction of study medication. These will be documented on the Baseline AE log. This list will be reviewed and compared to reported events throughout the study. *If the participant reports the same ongoing symptom (same severity) during subsequent visits, the symptom is not recorded as an Adverse Event (AE). If the event is new (not previously reported) or worsened, as determined by assessor, then the AE should be reported.*
- During each scheduled visit, the assessor will ask the participant how they feel and review the list of symptoms of concern (starting with the symptoms recorded at the previous visit). Any event that meets the above criteria for an AE/SAE/UP should be recorded. In the case of unresolved AEs, clinical staff will update the AE log with any follow-up information that will be gathered during their investigation.
- The site will receive the results of all blood work performed on study participants from the designated lab. If lab results meet the criteria described in the protocol as an AE and are considered clinically significant by the site clinician then an AE should be recorded. **Please see Box 1.**
  - Participants will be alerted of abnormal lab results and receive a recommendation to see their local provider. All abnormal lab results obtained at the baseline visit will be listed on the Baseline AE log. During follow-up visits, abnormal lab results will be listed as an AE *only if* the abnormal lab results:
    - Developed at follow-up (i.e. were not previously recorded at baseline).
    - Worsened in severity than what was previously recorded at baseline.
    - Or considered to be clinically significant.
- All AEs will be assessed to determine if they meet criteria for a Serious Adverse Event (SAE). If the AE is serious, then the SAE form is completed and appropriate reporting measures followed (see below). Investigators are encouraged to consult with the US Team, if they are uncertain how to classify an event.
- The list of participant's current medications will be reviewed and updated at every study visit, starting at baseline.
- If an event is discovered outside of the scheduled study visits, it should still be recorded accordingly.
- Action Taken will be determined by the assessors for all AEs that are Mild and Moderate and by Site PI or designee for SAEs and AEs that are severe, life-threatening or fatal.

**Box 1. Abnormal Lab Results**

|                            | A. Normal Lab Values                                      |
|----------------------------|------------------------------------------------------------------|
| Cholesterol (total) | to 5.7 mmol/L
[220 mg/dL]                                     |
| HDL                 | 1.04 – 1.55 mmol/L
[40 – 60 mg/dL]                            |
| HS CRP              | to 10 mg/L                                                       |
| CD4                 | 35.0-55.0% (from lymphocytes)                                    |
| HIV-1 RNA           | > 1,000 copies                                                   |
| Hemoglobin          | M: 130-160 g/L [13-16 g/dL]
F: 120-140 g/L [12-14 g/dL]       |
| Platelet            | 180 – 320 x 10  /L
[180,000-320,000/uL]           |
| eGFR (Crea)         | M: 53-97 mmol/L [0.6-1.1mg/dL]
F: 44-80 mmol/L [0.5-0.9mg/dL] |
| HCV Ag qualitative  | negative                                                         |
| HCV Ab              | negative                                                         |
| AST                 | M: to 37 units/L
F: to 31 units/L                             |
| ALT                 | M: to 40 units/L
F: to 31 units/L                             |

1. Laboratory results reviewed by study clinician and abnormal results (outside of normal values listed in column A) are identified.
2. If clinician determines abnormal lab results to be clinically significant, participant contacted by phone: result shared and participant referred to local provider.
3. Abnormal result registered as an AE.
4. If clinician determines abnormal lab results to be not clinically significant (for example slightly elevated AST and ALT in case of chronic hep C), result shared with participant during their next study visit, but not recorded as an AE.
5. In situations where laboratory values were deemed dangerously abnormal by study clinician, participant is alerted and asked to call emergency services.
6. As per Pavlov protocol, all participants will be provided with pre- and post-test HCV counseling. Post-test counseling will take place at the time of their next study visit.

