## 3.4 MEDICATION CONSIDERATIONS

### 3.4.A SYMPTOM MONITORING

To minimize medication risks, participants will be monitored for adverse effects at each study visit. Participant symptoms will be assessed at baseline and any chronic conditions or symptoms that existed prior to introduction of study medication will be documented using an electronic Baseline Event form. During each subsequent study visit, the RA will ask the participant how they feel and review the list of symptoms of concern, beginning with any symptoms recorded at the previous visit and including the four

most frequent side effects of zinc: abdominal pain, diarrhea, nausea, and vomiting. The RA will ask about any new symptoms experienced by the participant since the last study visit. Any event that meets the criteria for an adverse event (AE), serious adverse event (SAE), or unanticipated problem will be recorded using paper and electronic AE and/or SAE forms. The site will receive the results of all blood work performed on study participants. Any abnormal lab results that are deemed clinically significant by the clinical team will be recorded as an AE and/or SAE and the participant will be referred to their local medical provider. All baseline events, AE and SAE forms will be reviewed by the US and Russian teams. All events will be presented to and reviewed by the Data and Safety Monitoring Board (DSMB).

Participants will also be alerted of possible interactions between zinc and certain antibiotics and instructed to discontinue the study drug and contact the study team should they initiate a course of antibiotic medication.

Participants will be encouraged to contact study personnel or another health care provider if they experience any adverse effects. Furthermore, every two months a report will be generated of participants who report taking more than one pill per day, or for those whose pill count adherence was greater than 100% at their previous study visit. The report will be reviewed by the US Project Manager and the Russian study team. Any questions or concerns will be brought forth to the study PIs.

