### 3.6.B. BLOOD

This study requires the collection of 22 mL of blood at baseline, 6-, 12-, and 18-month study visits. Blood will be tested for hemoglobin, platelets, CD4 count, HCV antibody and qualitative viral load (baseline and 18-months only), HIV viral load, high sensitivity C-reactive protein (HS CRP), total and HDL cholesterol (baseline and 18-months only), eGFR (creatinine), AST/ALT, and zinc levels (baseline and 18-months only). Zinc level testing will be performed in batches at ImmunoBioService laboratory. The remainder of the testing will be conducted at the Pasteur Laboratory.

Plasma samples will be stored for biomarker testing. Dried blood spot cards will be spotted using 60µL of blood per spot (or 300µL per card) and saved to be used for phosphatidylethanol (PEth) alcohol

biomarker testing. The incorporation of PEth will provide complement to self-report for alcohol consumption.

Blood will be collected prior to the assessment at baseline, 6-, 12-, and 18-month study visits. For a blood draw to be considered successful, one EDTA (8 mL) and one SST (3 mL) tube both must be at least  $\frac{3}{4}$  full. If the draw is successful, participants will be provided with full compensation and continue with the standard ZINC visit procedures. If the blood draw is unsuccessful at the participant's baseline visit, the participant will receive partial (1/3) compensation. The participant has 30 days after completion of the Screener to complete the blood draw. The participant will be disenrolled after three unsuccessful blood draw attempts or if more than 30 days have passed. The participant will be provided with full compensation at the third or final attempt. If the blood draw is unsuccessful at a follow-up study visit, the participant will be given partial (1/2) compensation for completion of the assessment. The participant will have 7 days to complete the second blood draw attempt. If this attempt is unsuccessful, the third attempt will be done at the next study visit (medication only visit). The participant will be provided with full compensation at the third attempt. For blood draw attempts that occur outside of the 7-day window, sections on medications and past 24-hour activities will be reassessed.

The following algorithm will be followed at the 18-month study visit for retesting HCV Ab/VL:

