#### 4.5 Baseline Participant Characteristics

Descriptive statistics will be calculated for the following variables at baseline overall and stratified by randomized group: age, sex, heavy alcohol (past week), education, marital status, employment, VACS Index, CD4, Reynolds risk score, IL-6, D-dimer, sCD14, 16sRDNA , smoking status (current, ever, never), BMI, CVD, AST/ALT, FIB4, HCV (test), HVL, hemoglobin, platelets, eGFR, Blood pressure, Total cholesterol, HDL cholesterol, CRP, mother/father MI. For continuous variables, the following will be provided: median, mean, standard deviation, 0th, 25th, 50th, 75th, and 100th percentiles. For categorical variables, frequencies and proportions will be provided. For each primary and secondary outcome, descriptives will also be reported stratified by arm and follow-up time, (note, no testing will be done for any of the above).

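### Box 1 gives HIV-1 RNA above 1,000 copies as the normal value, so step 1 as written flags low viral loads and passes high ones (minor correction)

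*Supplement*

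**What the plan says.** Protocol section 6.2 points to Box 1 for the laboratory criteria. Box 1 has 12 rows and a single value column, A, headed as normal values. In the HIV-1 RNA row that column reads > 1,000 copies, with no volume unit. Step 1 of the procedure below the table is a review by the study clinician in which "abnormal results (outside of normal values listed in column A) are identified".

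Two sentences in section 6.2 depend on that flag and carry no condition of clinical significance. The rule on notification is: "Participants will be alerted of abnormal lab results and receive a recommendation to see their local provider". The second rule concerns what is written down before study medication starts, and it reads: "All abnormal lab results obtained at the baseline visit will be listed on the Baseline AE log".

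Recording an AE is conditional. Section 6.2 requires that the results meet the protocol's criteria and "are considered clinically significant by the site clinician then an AE should be recorded". Section 3.4.A agrees: "Any abnormal lab results that are deemed clinically significant by the clinical team will be recorded as an AE and/or SAE". Box 1 steps 2 to 4 apply the same filter: a clinically significant abnormality leads to a telephone call, a referral and an AE, while one that is not significant is shared at the next visit and not recorded as an AE. Step 5 covers values that the clinician considers dangerous.

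Viral load is measured at baseline, 6, 12 and 18 months (section 3.6.B).

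**The concern.** Participants are HIV-positive and ART-naïve at entry. In a table of normal values one expects the HIV-1 RNA row to give an upper limit, so that high viral loads are flagged. The printed entry does the opposite.

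What is at stake is a notification and logging rule. The consent process tells participants that "they would not receive any medical care (HIV or addiction) as part of the study", so the alert with advice to see a local provider is how this section passes a laboratory result on to care. A rule followed to the letter would send that alert for a low viral load and not for a high one. It would also leave high baseline values off the Baseline AE log, which section 6.2 uses as the comparator for events at follow-up.

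**Working it through.** The plan has no calculated figure to reproduce here. The check applies step 1 to the HIV-1 RNA row as written and then with the direction reversed.

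**Inputs**

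- Normal value in column A: > 1,000 copies (Box 1).
- Rule: abnormal means outside column A (Box 1, step 1).

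**Applying the rule to illustrative values**

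| Viral load (copies) | As written (normal is above 1,000) | Direction reversed (normal is 1,000 or below) |
|---|---|---|
| 50 | flagged | not flagged |
| 1,000 | flagged | not flagged |
| 1,001 | not flagged | flagged |
| 100,000 | not flagged | flagged |

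The two versions disagree on every value. The right-hand column assumes that 1,000 is the intended cut-off. The documents give no other.

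**How the other rows are written**

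- Upper limit only, written as *to* a value: 4 (total cholesterol, HS CRP, AST, ALT).
- Two-sided range: 5 (HDL, CD4, hemoglobin, platelets, creatinine).
- Negative: 2 (the two HCV tests).
- Inequality sign: 1 (HIV-1 RNA).
- Total: 4 + 5 + 2 + 1 = 12.

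The HIV-1 RNA row is the only one with an inequality sign. An upper limit in the table's own style would read *to* a value. The entry therefore looks like an abnormal threshold placed in the normal column, or a reversed sign. Which of these happened is inference. The literal effect is the same.

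**Do the later steps repair it?** Steps 2 to 4 act on results already identified as abnormal. They can discard a low value flagged in error, but they do not bring back a high value that step 1 passed. Step 5 could catch one, but only if the clinician judges it dangerous.

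**What does not depend on the flag.** Baseline viral load is tabulated in any case: SAP section 4.5 lists "HCV (test), HVL, hemoglobin, platelets, eGFR" among the baseline variables, where HVL is taken to be HIV viral load. The outcomes and models in SAP sections 5.1 and 5.2 do not use the Box 1 limit.

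**The case against.** **The sign may be a reading error, or a column may be missing.** The text was extracted from a PDF, and lettering a lone column A hints that a second column once existed. The extraction risk cannot be excluded, so the first action is to check the sign. A lost column would not change the finding: the entry stands in column A, and the steps refer to no other column.

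**High values may be listed as usual for this cohort.** In ART-naïve participants a low viral load is the unexpected result, and section 2.7 notes four enrolled participants later found to be HIV-negative. The documents do not give this rationale, and the table is not built on it. Both HCV rows list negative as normal, although step 4 uses chronic hepatitis C as its example of an abnormality that may not matter. Column A holds reference values and leaves context to the clinician.

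**Little follows from the slip.** This stands. Step 1 is itself a clinician's review, CD4 is flagged by its own row, participants already have documented HIV infection, and section 4.3 gives all of them a handout on HIV treatment services at baseline.

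**A stronger reading to avoid.** Section 6.2 lists newly developed abnormal results among the follow-up conditions for an AE. A reader might infer that viral suppression after starting ART would be recorded as an adverse event. The text does not support that: the parent statement in section 6.2, section 3.4.A and Box 1 steps 2 to 4 all make AE recording depend on clinical significance.

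**Conclusion.** The point holds as a minor correction. As written, one of 12 rows reverses the trigger for the participant alert and the Baseline AE log entry: viral loads of 1,000 copies or below are flagged and higher ones pass.

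The practical effect is small, for the reasons accepted above. A reader might go further and infer biased safety or efficacy results, or harm to participants. The documents support neither. The rule is the same in both arms, no efficacy analysis uses the limit, and baseline viral load is reported regardless. No count of affected participants can be given, because the documents contain no viral-load distribution.

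The conclusion assumes that the sign was extracted correctly and that step 1 is applied as worded. A clinician reading the row with ordinary judgement may never have followed it literally.

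**What to change.** Check the HIV-1 RNA row against the laboratory's reference sheet for direction, cut-off and volume unit. If the direction is confirmed wrong, rewrite the entry in the table's own style so that values above the laboratory's limit are the flagged range, for example *to 1,000 copies/mL*. The 1,000 and the per-mL unit both need confirmation, since the documents support 1,000 only through this entry and give no volume unit.

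The cost is one corrected table and a memo to the site, with no new tests. The corrected direction will add Baseline AE log entries and notices for participants above the limit. In an ART-naïve cohort that may be many, and the documents do not allow an estimate. Steps 2 and 4 already let the clinician sort them by significance.

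A clerical correction, separate from this finding, belongs in the same edit. The row labelled eGFR (Crea) holds creatinine ranges printed in mmol/L. At 88.4 micromol/L per mg/dL, the bracketed 0.6 to 1.1 mg/dL gives 0.6 × 88.4 = 53.0 and 1.1 × 88.4 = 97.2, and 0.5 to 0.9 mg/dL gives 0.5 × 88.4 = 44.2 and 0.9 × 88.4 = 79.6. The printed 53–97 and 44–80 are therefore micromol/L. Relabel the row as creatinine in that unit. The mg/dL brackets are usable and no flag is reversed. A micro sign lost in extraction is also possible here.
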